## Abstract

**Background:**

The poor relationship between doctors and patients is a long-standing, global problem. However, current interventions tend to focus on the training of physicians, while patient-targeted interventions still need to be improved. Considering that patients play a significant role in outpatient consultations, we developed a protocol to assess the effectiveness of the Patient Oriented Four Habits Model (POFHM) in improving doctor-patient relationships.

**Methods:**

A cross-sectional incomplete stepped-wedge cluster randomized trial design will be conducted in 8 primary healthcare institutions (PHCs). Following phase I of “usual care” as control measures for each PHC, either a patient- or doctor-only intervention will be implemented in phase II. In phase III, both patients and doctors will be involved in the intervention. This study will be conducted simultaneously in Nanling County and West Lake District. The primary outcomes will be evaluated after patients complete their visit: (1) patient literacy, (2) sense of control and (3) quality of doctor-patient communication. Finally, a mixed-effects model and subgroup analysis will be used to evaluate the effectiveness of the interventions.

**Discussion:**

Fostering good consultation habits for the patient is a potentially effective strategy to improve the quality of doctor-patient communication. This study evaluates the implementation process and develops a rigorous quality control manual using a theoretical domain framework under the collective culture of China. The results of this trial will provide substantial evidence of the effectiveness of patient-oriented interventions. The POFHM can benefit the PHCs and provide a reference for countries and regions where medical resources are scarce and collectivist cultures dominate.

**Trial registration:**

AsPredicted #107,282 on Sep 18, 2022; https://aspredicted.org/QST_MHW

**Supplementary Information:**

The online version contains supplementary material available at 10.1186/s12888-023-04948-w.

## Background

Conflicts between patients and doctors are still a prevalent problem worldwide [1, 2]. The incidence of workplace violence committed by patients and visitors against healthcare workers was prevalent globally, as high as 61.9% [1]. In China, 55.73% of healthcare workers and 33.70% of patients believe their relationship is tense [3].

Good communication is important for fixing difficult relationships between doctors and patients. Because both doctors and patients cite "good doctor-patient communication (DPC)" as the top factor of improvement in the doctor-patient relationship (DPR) [4, 5]. Besides, high-quality communication between patients and doctors has been proven to facilitate treatment adherence and self-management [6], improve health outcomes [7, 8] for patients and relieve burnout for doctors [7, 9]. Therefore, various intervention strategies to improve DPC have been proposed.

Various models and theories serve as a guide for research and practice. The American scholar Keller first proposed the E4 model of DPC (Engagement, Empathy, Education, Enlistment) and criticized the treatment process that centres on the disease [10]. Frankel then developed the Four Habits model (FHM) in 1996 [11], which involves investing in the beginning, eliciting the patient’s perspectives, demonstrating empathy, and investing in the end. In response to the call for an improved evaluation of communication skills, Makoul reported the SEGUE framework, a research-based checklist of DPC tasks [12]. SEGUE is an acronym for five areas (Set the stage, elicit information, give information, Understand the patient's perspective, and end the encounter), covering the entire medical interview [12]. From a theoretical perspective, shared decision-making (SDM) has recently become the focus of research. SDM emphasizes patient-centeredness, where patients and physicians are partners with equal power [13]. In addition, targeted theoretical tools have been developed for different scenarios, for example, prompt question lists for cancer patients [14] and patient activation for chronic patients [15].

Training for doctors and medical students has been the primary focus of DPC interventions and has developed a relatively mature training system from concept to practice [16]. Researchers now recognize the binary nature of the DPR and the critical role of patients [17]. However, most studies still tend to promote patient involvement in medical decision-making by educating physicians rather than patients [18], which is due in significant part to doctors’ dominant position in the treatment [19]. A scoping review reveals that nearly 50% of identified SDM interventions only targeted physicians [20]. Whereas the reliance on physician authority increases the risk of physicians acting as scapegoats. Previous studies have reported that patients who lack a sense of control tend to blame physicians for their health problems [21]. Furthermore, it is challenging to balance dominance and share decision-making with patients in communication if only doctors are skilled [22]. As the saying goes, "it takes two to tango", the expectation that effective communication could result from interventions aimed solely at either the doctor or the patient was unrealistic. One study found that SDM led to doubts about the doctor's competence for some patients, reflecting patient literacy heterogeneity [23]. In short, the process of DPC is dynamic in which doctors and patients interact. However, interventions to educate patients have been limited to date [24]. Therefore, the priority of our research protocol is to improve patient literacy, enhance the sense of control, and promote DPC through educating patients, followed by minor intervention with doctors.

The intervention design in this study was developed from the four-habit model (FHM). A longitudinal study has shown that FHM-based communication skills are closely and positively correlated with patient satisfaction scores [25]. Recently, based on a similar theoretical framework, Ming Tai-Seale’s team developed a multidimensional intervention called OpenComm to promote more open communication between patients and doctors [26]. Nevertheless, OpenComm focuses on communication content and ignores the importance of paying attention to emotions [26]. The competence of actively noticing emotional changes can be exercised through brief mindfulness intervention [27]. Based on the FHM, combined with mindfulness theory and the concept of patient-centeredness, we developed a complete framework including four good habits of patients and doctors, called Patient Oriented Four Habit Model (POFHM). The first habit (invest in the beginning) corresponds to patient role activation, an essential precursor to SDM, requiring knowledge, skills, and confidence in self-health management [28]. The second habit (focus on the greatest concern) corresponds to the question priority order, which was helpful in facilitating DPC [14, 29]. The third habit (focus on emotions) corresponds to emotional attention. The evidence suggests that over 90% of the studies reported a significant positive effect of brief mindfulness-based interventions on at least one health-related outcome [30]. The fourth habit (invest in the end) is a restatement, which helps the patient remember and follow the doctor's advice.

In addition, a consolidated framework to follow implementation science is crucial to bridging the gap between research evidence and practice [31]. Therefore, to ensure that the interventions work best in practice, the theoretical domain framework (TDF) was introduced to assess potential facilitators and barriers to intervention implementation [32]. Moreover, considering the characteristics of collectivist culture and Confucian culture, the role of the patient is often more than one person but a family [33, 34]. Therefore, the scope of the term "patient" in this study encompasses not only individuals receiving medical treatment but also their family members and friends.

In all, this study aims to evaluate the effectiveness of the POFHM intervention in primary health care institutions. POFHM is a promising intervention that integrates the four-habit theory, mindfulness theory, and patient-centered concept, providing education on four habits for mainly patients and then doctors during medical visits. The program ultimately expected to enhance the doctor-patient relationship in China, based on primary healthcare institutions. Initially, this study will evaluate the effectiveness of POFHM intervention, followed by conducting a manipulation check and process evaluation, in accordance with the implementation science framework [35]. Therefore, the results of POFHM can serve as a valuable reference for regions with limited medical resources and collectivist cultures.

In order to achieve full coverage of beneficial interventions and assess the impact of interventions, we will employ a stepped wedge cluster randomized trial (SW-CRT) [36]. The stepped wedge design enables the effectiveness of intervention programs to be tested systematically in a controlled manner. Firstly, clusters in a stepped wedge design effectively transition from the control group to the intervention group. At each phase, outcomes are evaluated among study participants in all clusters, ensuring that each cluster contributes data in both the control and intervention conditions [36]. Secondly, the stepped wedge design is advantageous as it permits researchers to progressively introduce and assess the various components of an intervention, while continuously optimizing the intervention [36]. Examples of stepped wedge investigations include the efficacy of 3 cancer pain guideline implementation strategies [37] and effects of a preschool-based sleep health literacy program [38]. The POFHM intervention is brief, and patients are unlikely to have repeat medical visit in the short term. Therefore, this study uses a cross-sectional and incomplete SW-CRT [39, 40], with a specific study design presented below.

## Methods

### Participants

#### Study sites

There were two primary reasons for selecting the implementation site. Firstly, we acknowledged that the economic level and the distinction between urban and rural areas may impact the efficacy of POFHM intervention. Secondly, we aim to verify that the intervention is effective for the majority of Chinese. To ensure that our sample is both representative and universal, we plan to recruit four PHCs in each of our chosen regions, Nanling County and West Lake District in China, which display significant differences. Please refer to Table 1 for an overview of the key components of the stepped wedge design.

**Table 1 Tab1:** Key characteristics of the POFHM trial

Trial characteristics	Definition
Cluster (unit of randomization)	Hospitals or Primary health care facilities (a total of 8)
Number of sequences (steps)	4 (2 hospitals per sequence)
Duration of trial	1 month
Number of measurement periods	7 (length of each period is 3 days)
Individuals	Patients (greater than or equal to 16 years old) visit a doctor at any time during the study
Timing of start of exposure	Patients are exposed to the process when they wait to be seen
Duration of exposure	Patients are exposed for a short period during their visit to the doctor
Measurement	Repeated measurements are from mostly different patients in each period; a tiny proportion of individuals may have repeat visits to the same hospital

The scope of the patient concept in this study extends beyond just the patients themselves and includes their family members and friends

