#### Control group

The essence of the incomplete stepped wedge design is that all primary healthcare facilities entered the study, starting with the control group and then entering different interventions in a randomly assigned sequence for the rest of the study period. During the control period (phase I), the doctors will complete routine consultations according to their habits. Volunteers will be responsible for maintaining order in the waiting room while the patient is waiting and conducting a questionnaire survey after the patient has completed the visit. The written guidance for doctors and the interactive question-and-answer training for patients will only be implemented when they enter the intervention period (phase II and III).

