### Randomization and blinding

#### Randomization

Each participating PHC stratified by region will be randomized to one of the predefined timelines (as depicted in Fig. 1) using a single sequence of random assignments. The research assistant will communicate intervention starting times with the participating PHCs.

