## Discussion

This paper has outlined the study design of the patient-oriented four habits model intervention and data collection. As far as we know, this study is the first to use an SW-CRT trial design to evaluate the effectiveness of a patient-oriented intervention designed to improve DPC. The conflict between patients and doctors is still an urgent problem, especially in China [61]. The intervention based on the patient-oriented four habits model is one of the effective measures to promote DPR [62]. It is despite the relative vulnerability of the patient during the medical visit [19]. However, access to more psychological resources and knowledge skills can increase the patient's sense of control during the visit [63], precisely what POFHM focuses on.

This trial has several important strengths. First, we developed universal interactive interventions based on previous research to provide practical patient training. In addition, to ensure that the interventions developed in this study work best in practice, the TDF was introduced to assess potential facilitators and barriers to intervention implementation. Second, the stepped-wedge design benefited all participating PHCs. Simultaneously, we utilized the stepped-wedge design to assess the difference in the effectiveness of a relationship intervention that involved either the doctor or the patient alone, versus involving both of them. Third, Subgroup analyses will provide a new perspective on understanding the heterogeneity of intervention effects in regions.

A potential limitation of this trial is that blindness is not allowed, as every PHC experienced a shift from a control group to an intervention group. However, it will be almost impossible for patients to be recruited repeatedly. Furthermore, we will reduce the personal impact of investigators and information bias by formulating a standard operating procedure. Another limitation of our study is the difficulty in sustaining the recruitment of volunteers to implement the intervention in routine situations. This emphasizes the need for further development of an interactive voice electronic app.

In conclusion, this study will provide helpful information on the effectiveness and universality of the patient-oriented, doctor-supported intervention.

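### As Table 1 is written, hospitals that step together appear to share the same single intervention, so patient-only and doctor-only start at different steps; splitting each pair would sharpen their comparison at almost no cost

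*Protocol article*

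**What the plan says.** Table 1 (Study sites) lists the clusters as "Hospitals or Primary health care facilities (a total of 8"), the number of sequences (steps) as "4 (2 hospitals per sequence"), and the measurement periods as "7 (length of each period is 3 days"). The same section states that "we plan to recruit four PHCs in each of our chosen regions".

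The conditions are described in three places:
- Abstract, Methods: "either a patient- or doctor-only intervention will be implemented in phase II", with both parties involved in phase III.
- Control group: all PHCs start in control, "then entering different interventions in a randomly assigned sequence for the rest of the study period".
- Randomization: each PHC, stratified by region, is "randomized to one of the predefined timelines" shown in Fig. 1.

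The Discussion counts as a strength that the design is used to "assess the difference in the effectiveness of a relationship intervention that involved either the doctor or the patient alone, versus involving both of them". The Statistical analysis section plans a mixed model for the three interventions, with PHC random and time fixed.

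**The concern.** In a stepped-wedge trial a sequence is the full ordered set of conditions that a cluster follows, and the Control group section uses the word that way. If there are four sequences, each is one step, and each holds two hospitals, then both hospitals on a step have the same path, including the same single intervention in phase II. I-P and I-D are then never introduced side by side. Which single intervention a hospital gets is partly tied to when it gets it. The model has to separate the two through estimated period effects and the differences between PHCs.

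At stake is the precision of the comparisons among the three interventions, which are a declared use of the design. The loss would be avoidable, because the same hospitals, periods and patients can be arranged so that both types start at every step.

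**Working it through.** **1. The plan's own count.** The Sample size section gives 8 clusters, 53 patients per site per 3-day interval, and 1272 patients. 8 × 3 × 53 = 1272, so the calculation implies three measured cells per PHC: control, single, both. Four cells would give 8 × 4 × 53 = 1696. Also 1272 / 0.8 = 1590, the stated target. The 80% power for a 0.13 difference cannot be reproduced because no SD is given, so results below are in SD units.

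**2. Layout (assumption).** Four steps one period apart with three consecutive cells fill 3 + 3 = 6 periods. Table 1 has 7, so I allow one unmeasured period per PHC (4 + 3 = 7), placed either before or after the single intervention. I-P is on two steps and I-D on two. On the unsplit reading both hospitals of a step share the type. Orders: alternating (P, D, P, D) or blocked (P, P, D, D). The regional stratification puts one hospital of each region on each step.

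**3. Model.** Random PHC, fixed period, effects for I-P, I-D and both (I-B). The cluster autocorrelation is 1, as the Sample size section makes no adjustment for it. With total variance 1, τ² = 0.034 and the within-cell variance is σ² = (1 − 0.034)/53 = 0.01823. The variance of a contrast c is c′(X′V⁻¹X)⁻¹c, where V has σ² + τ² on the diagonal and τ² between cells of the same PHC.

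**4. Pairs split, common period effects.** The two hospitals of a step differ only in the single-intervention cell. Taking the difference within each of the 4 pairs removes the period effects:

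Var(I-P − I-D) = 2σ² / {4[1 − τ²/(σ² + 3τ²)]}

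σ² + 3τ² = 0.01823 + 0.102 = 0.12023; τ²/0.12023 = 0.2828; variance = 0.03645/(4 × 0.7172) = 0.01271; SE = 0.113.

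**5. Pairs not split.** Solving the model in step 3 numerically gives these SEs (SD units):

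| Contrast | Unmeasured period | Alternating | Blocked | Split |
|---|---|---|---|---|
| I-P vs I-D | either | 0.188 | 0.204 | 0.113 |
| I-B vs I-P | before single | 0.143 | 0.164 | 0.112 |
| I-B vs I-D | before single | 0.128 | 0.121 | 0.112 |
| I-B vs I-P | after single | 0.186 | 0.222 | 0.159 |
| I-B vs I-D | after single | 0.168 | 0.154 | 0.159 |
| I-B vs control | either | 0.205 | 0.223 | 0.203 |

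For I-P vs I-D the reduction is 1 − 0.113/0.188 = 40% to 1 − 0.113/0.204 = 45%.

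**6. Single versus both, averaged.** Blocked, unmeasured period after the single: (0.222² + 0.154²)/(2 × 0.159²) = 0.0730/0.0506 = 1.44. The average variance is 1.44 times the split value, although I-B vs I-D alone is about 3% more precise unsplit (0.154 against 0.159). The same ratio for the other columns is 1.23 (alternating, after), 1.46 (alternating, before) and 1.65 (blocked, before). With a cluster autocorrelation of 0.8 it stays above 1 (1.24 to 1.99, including the order in step 7).

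**7. Period effects that differ by region.** Each step's pair now spans two sets of period effects, so the pairing no longer cancels them. The split SE for I-P vs I-D becomes 0.186, against 0.188 (alternating, 1% smaller) and 0.204 (blocked, 9% smaller). The remaining order, one type on steps 1 and 4 and the other on 2 and 3, goes from 0.2724 to 0.2357, or 1 − 0.2357/0.2724 = 13.5%. So the gain is about 0-14%.

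**The case against.** The strongest objection is to the premise. No sentence says which single intervention each hospital of a step receives. That is left to Fig. 1, and the row label in Table 1, which sets steps beside sequences, may count crossover times only. If the pairs are already split, there is no loss of precision, only a misleading table entry. This stands: a reader might take it as established that the two types never start together, but the documents support that only as the natural reading of Table 1.

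The second objection is to the size. Each step's pair is one hospital from each region, and the Study sites section itself says that the regions differ significantly. The large gain needs both to share one set of period effects. The analysis section says only that time is fixed, so the 0.113 is a best case and the 0-14% range applies if the regions drift differently. This also stands.

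Third, a reader might infer that every single-versus-both comparison suffers. Step 6 shows one that does not. The largest gain is for I-P vs I-D, whereas the Discussion names either alone against both. The main comparison of the full intervention with control hardly depends on the choice. The regional subgroup analyses gain nothing, since each region has one hospital per step.

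What remains is that, under the model the plan states, splitting the pairs improves these contrasts on average without more hospitals, periods or patients.

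**Conclusion.** The point holds as a conditional one. If Table 1 means what it says, the plan gives up precision between I-P and I-D that it could have had: an SE of 0.188-0.204 SD where 0.113 SD was available under common period effects. The average variance of the single-versus-both contrasts is also higher than it need be. If period effects differ by region, the I-P vs I-D loss is small, about 0-14% of the SE. I-B vs control is little affected (0.205-0.223 against 0.203).

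This rests on the assumed layout (three cells per PHC over 7 periods, one of them unmeasured), the 2:2 spread of types over steps, an ICC of 0.034 and 53 patients per cell. It does not show that the trial is underpowered for any contrast. Without an SD for the 0.13 difference, these SEs cannot be turned into power. Because the change is so cheap it should be made, or the table clarified, but it is not a flaw that undermines the trial.

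**What to change.** Before randomisation, keep the step times and whatever I-P/I-D order is planned in one region, and use the mirror order (I-P and I-D swapped) in the other. Every step then has one I-P and one I-D hospital, and each region has two of each. Randomise the four PHCs of each region to that region's four timelines, which respects the planned stratification. No particular order, such as strict alternation, needs to be prescribed: with region-specific period effects an alternating order can be less precise than a blocked one in some layouts. Mirroring leaves I-P vs I-D precision within a region unchanged, since only the labels swap.

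Restate Table 1 as 4 steps, 8 timelines, 1 hospital each, and say in the Randomization section which single intervention each timeline contains. If Fig. 1 already splits the pairs, only Table 1 needs correcting.

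Cost: a revised allocation table, with the same PHCs, periods and patients. The one practical burden is that both single interventions must be ready at the same step.
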